### Sample size

41 centres per arm (from 10 to 14 local authorities), each recruiting 12 parents on average (4 parents from 3 programmes, 984 parents in total) will provide 90% power to detect a small standardised effect size of 0.27 as per previous trials (25–28) for BMI z-score at a 5% significance level, assuming an ICC of 0.03 (16, 25, 29–31) to account for clustering by centre, a coefficient of variation of 0.48 to account for variation in centre recruitment and 20% loss to follow-up.^18^

### Withdrawal of consent

Centres and/or local authorities can withdraw at any point during the trial. Data collected up to the time of withdrawal will be retained for analysis and data from parents and staff will still be collected provided they have not withdrawn consent themselves. Centres may stop delivering the HENRY programme during the trial period independently from the trial (eg, centre closures, restructuring). Trial procedures will continue in this eventuality and all recruited parents and staff will remain in the trial (and data will continue to be collected from them) unless they actively withdraw. Where parents or staff wish to withdraw, there will be clarification whether this is withdrawal from short-term trial data collection, or from medium-term trial data collection (using routine data) or a combination of these. Non-attendance at HENRY intervention sessions are not classed as a withdrawal from the trial. All parents who withdraw from HENRY intervention or who do not attend the intervention will still be followed up for data collection unless they specifically express a wish to withdraw from trial processes.

### Data analysis plan

Analysis will be carried out on the intention-to-treat (ITT) population defined as all local authorities/centres randomised and all parents registered to the trial, regardless of adherence to the protocol, withdrawal of consent or losses to follow-up. A two-sided 5% significance level will be used for statistical endpoint comparisons. No interim analyses are planned, except for safety data that are required for review by the data monitoring and ethics committee.

The flow of local authorities, centres and participants through the trial will be presented in a Consolidated Standards of Reporting Trials diagram.

The primary outcome, child age-adjusted and sex-adjusted BMI (BMI z-score) will be analysed using a multilevel linear regression with children nested within centres and centres treated as a random effect. The model will be adjusted for the following fixed effects: centre-level stratification factors, important parent-level and child-level covariates (eg, baseline child BMI z-score and sex, parent BMI), and other relevant known predictors of outcome. Missing data will be imputed at the individual participant level where appropriate. Estimated mean differences will be reported with 95% confidence intervals, p values and ICCs. Model diagnostics will be used to check the underlying assumptions of the model and alternative methodology will be used if required.

Sensitivity analyses of the primary endpoint will be conducted to assess the impact of missing data, the choice of imputation model and the missing at random assumption, as appropriate. If contamination between intervention and control centres is identified, a sensitivity analysis excluding the relevant control centres will be conducted.

If numbers allow, exploratory subgroup analysis will examine differences in intervention effect between different socioeconomic and ethnic groups, and also between online and face-to-face delivery of HENRY.

For secondary outcomes, summary statistics will be presented at baseline and 12 months post parent registration overall and by arm (means, SD, medians, minimum, maximum and quartiles for continuous variables, and counts and percentages for categorical variables).

Medium-term analysis (3 years post parent recruitment) will compare regional population-level BMI z-score (trial local authority areas) with that of trial participants and siblings (HENRY and control) to investigate differences in BMI z-score. Analysis will use the same approach as the primary outcome for different outcome types, using multilevel regression with multiple imputation for missing data.

### Internal pilot

Descriptive analysis of the internal pilot against progression criteria will take place at three separate time points as described in table 2 and discussed with the trial steering committee (TSC) to inform a decision on the modification or continuation of the trial.

**Table 2 T2:** Internal pilot progression criteria

Criteria	Green (go)	Amber (review)	Red (stop)
Centre recruitment: Centres open within 12 months of starting centre recruitment (including data up to the end of month 19). A centre will be defined as open if it has been randomised and is open to recruitment.	≥54	42–53	<42
Parent recruitment: Average number of parents recruited per programme/equivalent (including data up to the end of month 23, allowing for 6 months of parent recruitment).	≥4	3–<4	<3
HENRY programme delivery: Percentage of intervention centres having started delivery of at least one programme (including data up to the end of month 27, allowing for 18 months from starting centre recruitment). The denominator will include all centres allocated to the intervention arm. The numerator will be all of those intervention centres that have started to deliver at least one programme, defined as delivering at least one session to parents.	≥80%	50%–80%	<50%

HENRY, Health, Exercise and Nutrition for the Really Young.

### Economic evaluation

Economic analysis will be conducted in three stages: (1) 12-month short-term within-trial cost-effectiveness analysis of the incremental cost per unit change in BMI z-score; (2) 3-year cost-effectiveness analysis of the incremental cost per unit change in BMI z-score with additional routinely collected NCMP data and (3) longer-term estimates of BMI z-score trajectories and healthcare use using a matched cohort of Millennium Cohort Study (MCS) participants.^21^ The MCS dataset provides a unique and high-quality resource that enables us to project long-term BMI trajectories and healthcare resource use into early adulthood at the individual level.

The overarching aim of the economic analysis is to reduce decision uncertainty about whether or not HENRY should be commissioned. As we increase the time horizon of the analysis, it is anticipated that decision uncertainty will be reduced in the sense that it will become much clearer whether or not HENRY should be commissioned. Primary analyses will adopt an NHS and local authority perspective. Supplementary analyses will adopt a wider societal perspective by assessing household costs and productivity losses. Spill-over benefits to parents will also be captured by calculating differences between the two treatment groups in terms of quality-adjusted life-years over 12 months. Utility scores will be measured using both the EQ-5D-5L^22^ and the ICECAP-A.^23^ All analyses will be conducted using the ITT population. Seemingly unrelated regression will be used to account for the correlation between costs and outcome measures. Multilevel models will be used to account for children nested within centres. Decisions about which child-level, parent-level and centre-level covariates to include in the models will be made after assessing differences in baseline characteristics, and through discussion with the trial statisticians. Patterns (and reasons) of missing data will be investigated in collaboration with the trial statisticians and appropriate imputation techniques will be used. Supplementary analyses will assess whether there are differences in costs and effectiveness by the intervention delivery method by including an interaction term between method (ie, online vs face to face) and the treatment variable. In order to address whether or not the intervention is equally cost-effective among children living in the most deprived areas and households, analyses will also use interaction terms for household-level socioeconomic status and for area-level deprivation (≤10%/>10% ranking within Index of Multiple Deprivation at the lower super output area). To assess whether a parent/carer’s propensity to commit to engage with HENRY was affected by their attitude to risk or perceptions about their long-term health prospects, analyses will also use interaction terms for self-reported measures of these factors based on questions used in the English Longitudinal Study of Ageing^24^ and German Socioeconomic Panel.^25^

Uncertainty in our cost-effectiveness estimates will be characterised by presenting bootstrapped estimates on CEACs using a wide range of different cost-effectiveness thresholds (£/BMI change). While acknowledging that the true WTP threshold is unobserved, the choice of thresholds would be based on existing literature on the cost-effectiveness of comparable interventions and expert opinion. A version of the CEAC which shows the probability of the intervention being cost saving (ie, in the SE quadrant), regardless of the willingness-to-pay (WTP) threshold, will also be presented. One way sensitivity analyses will include an assessment of varying the intervention cost and of using alternative methods and approaches to matching the trial data with participants in the MCS dataset. Results for all economic analyses will be reported in accordance with the Consolidated Health Economic Evaluation Reporting Standards guidelines^26^ using Stata (StataCorp, V.18.0) and/or R (R V.4.3).

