#### Programme delivery to parents

The ‘Right from the Start’ programme is delivered to groups of approximately 8–10 parents over 8 sessions. Each interactive session focuses on a separate theme and includes resources for families to take home. Each centre delivers 2–3 ‘Right from the Start’ group programmes per year, each consisting of 8×2 hours sessions.

Programmes can be delivered remotely or face to face. We will include both delivery modes in the proposed research. This will allow us to be flexible depending on external issues, in addition to supporting an evaluation of a pragmatic intervention. Our analysis plan includes consideration of different delivery approaches.

Parents with a child aged up to 5 years are eligible to attend HENRY. The programme can be tailored to specific groups or parents, for example, to align with dietary practices for different ethnicities or religion. Language needs are addressed locally depending on the population needs, with some areas providing dedicated support. Without this, the other approach is to invite parents to attend with a friend or family member to support translation and other activities. Although considered to be a universal programme, practitioners often refer families ‘at risk’ to HENRY and the delivery model within children’s centres allows parents from the most deprived neighbourhoods to attend.

Parents receive a standardised manual as part of the programme. To monitor adherence, session attendance will be recorded for parents who consent.

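### The interaction terms offered to assess propensity to engage with HENRY most naturally estimate effect modification of cost and BMI z-score, and so do not estimate engagement

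*Protocol article*

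**What the plan says.** In the Economic evaluation section, the question is whether a parent's "propensity to commit to engage with HENRY was affected by their attitude to risk or perceptions about their long-term health prospects". The method, in the same sentence, is that "analyses will also use interaction terms for self-reported measures of these factors".

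The same section describes the analyses to which such terms would belong. On model form: "Seemingly unrelated regression will be used to account for the correlation between costs and outcome measures", with multilevel models for children within centres. On population: "All analyses will be conducted using the ITT population". The within-trial effect measure is BMI z-score: "within-trial cost-effectiveness analysis of the incremental cost per unit change in BMI z-score". The first use of an interaction in the paragraph looks at "differences in costs and effectiveness by the intervention delivery method by including an interaction term between method" and the treatment variable. The next use concerns whether cost-effectiveness is equal across levels of deprivation.

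On engagement data, Programme delivery to parents says: "To monitor adherence, session attendance will be recorded for parents who consent". The Systems-based process evaluation section plans to summarise attendance and drop-out by centre and overall. Neither place links attendance to the risk-attitude or health-expectation items.

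**The concern.** Question and method point at different quantities. The question treats engagement as the thing to be explained, with risk attitude and perceived health prospects as the explanatory factors. A factor-by-treatment term in a model of cost or BMI z-score asks something else: whether the effect of allocation on that outcome differs by risk attitude. That difference can arise because some parents attend more, because some respond more to the same attendance, or both. Engagement with HENRY sessions also exists only in the intervention arm, so a between-arm interaction has the wrong structure for it.

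At stake is the meaning of one supplementary result. If interaction estimates are reported under an aim about engagement, neither a null nor a positive finding would answer that aim. The data that bear on it more directly would meanwhile be summarised only descriptively.

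**Working it through.** The plan states no figure for this analysis, so there is none to reproduce. The main check is logical; the numbers only illustrate it.

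**1. Question against estimand.**
- Quantity to be explained: propensity to engage (Economic evaluation).
- Dependent variables of the economic models described: costs and outcome measures.
- Meaning of an interaction in the preceding sentences: a difference in cost or effectiveness between levels of a factor.
- Models described with engagement as the dependent variable: none.

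**2. Can the interaction move without engagement, and engagement without the interaction?** A simulation used 984 parents (protocol total), half per arm, unclustered, 2,000 runs per scenario. All other values are assumptions: a standard normal risk-attitude score, attendance yes/no with log-odds 0.5 plus a slope, and an outcome with SD 1. The interaction test is treatment by risk attitude on the outcome. The direct test is attendance on risk attitude in the HENRY arm.

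| Scenario | Interaction significant | Direct test significant |
|---|---|---|
| A. Attendance depends on risk attitude (0.8 log-odds per SD), programme has no effect | 5.1% | 100% |
| B. As A, with an effect of 0.27 SD among attenders | 11.5% | 100% |
| C. Attendance unrelated to risk attitude, effect among attenders modified by 0.2 SD per SD | 49.9% | 4.5% |
| D. Neither | 5.1% | 4.7% |

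In A the interaction stays at chance level although attendance differs strongly. In C it is significant in half the runs although attendance does not differ at all.

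**3. Illustrative power, interaction in BMI z-score.** From the Sample size section: 984 × 0.8 = 787 followed up, ICC 0.03, standardised effect 0.27. Assumed: two equal halves by risk attitude, and an effect proportional to attendance with 0.27 at full attendance.
- SE = 4/√787 × √(1 − 0.03) = 0.140, two-sided 5%.
- Attendance 80% v 50%: interaction = 0.27 × 0.30 = 0.081, power 8.9%.
- Attendance 80% v 65%: interaction = 0.27 × 0.15 = 0.0405, power 6.0%.
- Adjusting for baseline BMI z-score multiplies the SE by √(1 − r²). With assumed r = 0.7 the SE is 0.100 and power for 0.081 is 13%; with r = 0.8 the SE is 0.084 and power is 16%.

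**4. Illustrative power, attendance modelled directly.** HENRY arm 984/2 = 492. Design effect 1 + (12 − 1) × 0.03 = 1.33, borrowing the BMI z-score ICC because no attendance ICC is given. Effective number per half = 492/2/1.33 = 185. SE = √[(p₁(1 − p₁) + p₂(1 − p₂))/effective number per half].

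| Assumed attendance consent and ICC | Effective number per half | 80% v 50% | 80% v 65% |
|---|---|---|---|
| 100%, ICC 0.03 | 185 | >99% | 91% |
| 70%, ICC 0.03 | 129 | >99% | 78% |
| 50%, ICC 0.03 | 92 | 99.5% | 64% |
| 50%, ICC 0.10 (design effect 2.1) | 59 | 95% | 45% |

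Using the protocol's coefficient of variation of 0.48 with 12 per centre gives a design effect of 1 + ((1 + 0.48²) × 12 − 1) × 0.03 = 1.41. At full consent this lowers 91% to 89%.

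**The case against.** **The dependent variable is inferred.** A reader might take it that the protocol states these are interactions with treatment in models of cost and BMI z-score, and conclude that the question cannot be answered as planned. The sentence names neither a dependent variable nor treatment as the interacting factor. Both are read across from neighbouring sentences, and a condensed article may leave them to a fuller economic analysis plan. This stands: the conclusion is conditional on the natural reading.

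**The cost model may carry some engagement information.** If intervention cost were apportioned by individual attendance, a cost interaction would reflect engagement indirectly. The article does not say whether it will be. The power figures cover BMI z-score only, so they do not show that the cost half of the model is uninformative. This also stands.

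**The power contrast is soft.** Attendance rates, proportionality of effect, consent, the attendance ICC and the baseline correlation are all assumed, and 0.27 is the design's detectable effect, not a stated effect at full attendance. Clustering is also handled differently on the two sides: a factor of 0.97 on the variance for the interaction, 1.33 or more for the direct test. The ranking holds across the ranges tried, but no single pair of figures should be relied on.

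**Attendance is not commitment.** A reader might infer that attendance records settle the stated question. They do not. Under Eligibility criteria, parents at intervention centres must already be willing to attend, so attendance shows what enrolled parents did after committing. The interaction terms do not address the decision to sign up either.

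**A misreading of a null is not foretold.** A reader might also infer that a null interaction will be reported as no effect on engagement. The article sets no such interpretation rule; this is only a risk created by the wording.

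**Conclusion.** The concern holds in a limited form. On the most natural reading, the planned terms estimate whether the effect on cost or BMI z-score differs by risk attitude or health expectations. They do not estimate propensity to engage, and no model described has engagement as its outcome, although attendance is recorded. That conclusion rests on the reading of one sentence in its paragraph, not on any figure.

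As to size, and for illustration only, power is roughly 6% to 16% for the BMI z-score interaction against about 45% to over 99% for a direct attendance model, depending on consent, ICC and the attendance difference. The primary outcome, the main cost-effectiveness estimate and the sample size are unaffected. This is a cheap improvement to a supplementary economic analysis.

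**What to change.** 1. Restate the interaction analysis as what it estimates: effect modification of cost and BMI z-score by risk attitude and health expectations. Name the dependent variables and the interacting factor.
2. For engagement, add a multilevel regression in the HENRY arm of sessions attended (0 to 8) on the baseline risk-attitude and health-expectation items, with centre as a random effect. Report it as attendance among enrolled parents.

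The cost is one reworded sentence and one extra regression on data the article already plans to collect, with no change to design or sample size. There are two downsides. The regression is limited to parents who consent to share attendance, so the consent rate should be reported beside it. And it does not address the decision to sign up.

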**Methods and analysis:**

This is a multicentre, open-labelled, two-group, prospective, cluster randomised controlled trial, with cost-effectiveness analysis, systems-based process evaluation and internal pilot. Primary analysis will compare body mass index (BMI) z-score at 12 months in children (n=984) whose parents have attended HENRY to those who have not attended. Secondary outcomes include parent and staff BMI and waist circumference, parenting efficacy, feeding, eating habits, quality of life, resource use and medium term (3 years) BMI z-scores (child and siblings). 82 centres in ~14 local authority areas will be randomised (1:1) to receive HENRY or continue with standard practice. Intention-to-treat analysis will compare outcomes using mixed effects linear regression. Economic evaluation will estimate a within-trial calculation of cost-per unit change in BMI z-score and longer-term trajectories to determine lifelong cost savings (long-term outcomes). A systems process evaluation will explore whether (and how) implementation of HENRY impacts (and is impacted by) the early years obesity system. An established parent advisory group will support delivery and dissemination.

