#### Economic evaluation objectives

To explore the long-term effects on child BMI.To determine whether HENRY provides an overall cost saving (eg, to the NHS).

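### The probability labelled 'cost saving' is defined as the SE quadrant, which is dominance, so it is a lower bound for the probability that HENRY saves money

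*Protocol article*

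**What the plan says.** Under Economic evaluation objectives, the protocol article sets the aim "To determine whether HENRY provides an overall cost saving (eg, to the NHS"). No condition on effectiveness is attached.

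Under Economic evaluation, the first two stages (12 months and 3 years) estimate the "incremental cost per unit change in BMI z-score". The third stage projects BMI z-score trajectories and healthcare use from a matched cohort. On perspective the section states: "Primary analyses will adopt an NHS and local authority perspective".

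Uncertainty is to be shown by "presenting bootstrapped estimates on CEACs using a wide range of different cost-effectiveness thresholds (£/BMI change"). In addition there will be a variant of the curve giving "the probability of the intervention being cost saving (ie, in the SE quadrant), regardless of the willingness-to-pay (WTP) threshold".

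The abstract links the cost question to a different piece of work: "longer-term trajectories to determine lifelong cost savings (long-term outcomes").

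**The concern.** The 'ie' in that sentence equates two different events. An intervention saves cost when its incremental cost is negative, whatever happens to the outcome. It lies in the SE quadrant when its incremental cost is negative and it is also more effective. The second event is contained in the first.

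This is the only probability in the article that carries the label 'cost saving', and cost saving is a declared objective. A commissioner would naturally read it as the chance that HENRY saves money. Computed as defined, it leaves out every bootstrap replicate in which HENRY is cheaper but the BMI z-score is not reduced. This is not a detail left to a later plan, because the article gives a definition and the definition does not match its label.

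**Working it through.** **1. Definitions.** Let dC be incremental cost and dE the incremental benefit, taken as BMI z-score reduction so that east is favourable.

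- Cost saving: P(dC < 0) = P(SE) + P(SW).
- Dominance: P(dC < 0 and dE > 0) = P(SE).
- Gap: P(dC < 0) − P(SE) = P(SW), which is never negative.

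So P(SE) is a lower bound for the probability of cost saving.

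**2. Inputs for sizing the gap.** The article gives no cost, cost SE or probability here, so there is no stated figure to reproduce for the display itself. The precision of the effect can be taken from the Sample size section: 41 centres per arm, 12 parents per centre, 20% loss, ICC 0.03, coefficient of variation 0.48, effect 0.27 SD, 90% power. The two-sided 5% level is in the Data analysis plan.

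- Analysed per centre: 12 × 0.8 = 9.6.
- Design effect: 1 + ((1 + 0.48²) × 9.6 − 1) × 0.03 = 1.324.
- Effective n per arm: 41 × 9.6 / 1.324 = 297.
- SE of the standardised difference: √(2/297) = 0.082.
- Power at 0.27: 0.908 (normal), or 0.902 (t on 80 df). The stated 90% reproduces, so 0.082 is a fair scale for the effect axis.

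**3. Simplest case.** Assume the bootstrap cloud is normal, cost and effect are uncorrelated, and incremental cost is centred on zero, so that P(dC < 0) = 0.50. For an effect estimate d in SD units, P(SE) = 0.50 × Φ(d / 0.082).

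**4. Range.** Using a bivariate normal, let incremental cost be −1, 0 or +1 of its own SE, and let the correlation between cost and benefit be −0.3, 0 or 0.3. These values are assumptions.

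| Effect estimate (SD) | P(dC < 0), simplest case | P(SE), simplest case | Gap, simplest case | Gap over assumed range (percentage points) |
|---|---|---|---|---|
| 0.27 (design) | 0.500 | 0.500 | 0.000 | below 0.1 |
| 0.135 | 0.500 | 0.475 | 0.025 | 0.2 to 4.8 |
| 0.08 | 0.500 | 0.418 | 0.082 | 1.1 to 15.4 |
| 0 | 0.500 | 0.250 | 0.250 | 5 to 45 |

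**5. Relation to the ordinary CEAC.** The CEAC at threshold λ is P(λ·dE − dC > 0). At λ = 0 this is P(dC < 0). In a simulated example (effect 0.135 SD, mean incremental cost £20 with SE £60, no correlation), the CEAC at £0 was 0.368 and P(SE) was 0.350. If £0 is on the plotted axis, the report would contain two different values that could both be read as the probability of cost saving.

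**The case against.** The strongest reply is that the sentence makes sense as a dominance probability under a loose label. Being favoured at every non-negative threshold is a property of SE and not of SW, so the words "regardless of the willingness-to-pay (WTP) threshold, will also be presented" describe dominance well. The bracket also tells the reader which quadrant is counted. This stands as an account of what the authors probably meant, but it confirms that the label is the part to change.

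Three stronger readings are tempting, and the document does not support them.

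- *The cost-saving objective will be answered with the wrong number.* Nothing makes this display the sole or deciding answer. Incremental cost is estimated in any case as the numerator of the ratio, the abstract assigns lifelong savings to the longer-term trajectories, and the third stage estimates later healthcare use. An ordinary CEAC would also give P(dC < 0) if £0 is among its thresholds, which the article does not say.
- *Because a fall in BMI z-score is the benefit, SE would be the quadrant with heavier children.* The article states no axis direction, but it treats SE as favourable and pays per unit of BMI change, which makes sense only if change is counted as benefit. The direction should be stated; it is not shown to be reversed.
- *A threshold-free probability cannot be a version of the CEAC.* It can be drawn as a flat line. That is a matter of presentation.

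It is also fair to say that the gap vanishes if HENRY works as designed, and that the error runs one way only: it cannot produce an inflated claim that HENRY saves money.

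**Conclusion.** The point holds as a matter of definition and labelling. The figure called the probability of being cost saving is the probability of dominance, and it understates the probability of cost saving by P(SW).

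The size depends on the effect. The gap is negligible near 0.27 SD, at most about 5 points at half that, and 5 to 45 points at zero effect. Small effects cannot be set aside, since the article's Introduction describes the benefits of such programmes as generally limited and variable.

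These sizes rest on a normal approximation, on the assumed cost and correlation ranges, and on an SE of 0.082 in SD units. That SE is for 12 months and takes no account of baseline adjustment, which would normally narrow it. Applying it to z-score units would need an SD of 1. The direction of the error depends on none of these assumptions. The primary analysis and the sample size are untouched.

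**What to change.** In the Economic evaluation section:

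1. State that incremental effect is BMI z-score reduction, so that east on the plane means benefit.
2. Rename the SE figure 'probability dominant', defined as P(incremental cost < 0 and BMI z-score reduced).
3. Report P(incremental cost < 0), that is SE plus SW, as 'probability cost saving', against the objective of that name.
4. Keep the ordinary CEAC for the threshold-dependent result.

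The cost is a change of wording and one extra count from bootstrap replicates already planned. No new data or modelling is needed.
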